## Abstract

**Background:**

Fractures of the distal radius represent the most common fracture in elderly patients, and often indicate the onset of symptomatic osteoporosis. A variety of treatment options is available, including closed reduction and plaster casting, K-wire-stabilization, external fixation and open reduction and internal fixation (ORIF) with volar locked plating. The latter is widely promoted by clinicians and hardware manufacturers. Closed reduction and cast stabilization for six weeks is a simple, convenient, and ubiquitously available intervention. In contrast, ORIF requires hospitalization, but allows for functional rehabilitation.

Given the lack of randomized controlled trials, it remains unclear whether ORIF leads to better functional outcomes one year after injury than closed reduction and casting.

**Methods/Design:**

ORCHID (Open reduction and internal fixation versus casting for highly comminuted intra-articular fractures of the distal radius) is a pragmatic, randomized, multi-center, clinical trial with two parallel treatment arms. It is planned to include 504 patients in 15 participating centers throughout Germany over a three-year period. Patients are allocated by a central web-based randomization tool.

The primary objective is to determine differences in the Short Form 36 (SF-36) Physical Component Score (PCS) between volar locked plating and closed reduction and casting of intraarticular, comminuted distal radius fractures in patients > 65 years of age one year after the fracture. Secondary outcomes include differences in other SF-36 dimensions, the EuroQol-5D questionnaire, the Disability of the Arm, Shoulder, and Hand (DASH) instrument. Also, the range of motion in the affected wrist, activities of daily living, complications (including secondary ORIF and revision surgery), as well as serious adverse events will be assessed. Data obtained during the trial will be used for later health-economic evaluations. The trial architecture involves a central statistical unit, an independent monitoring institute, and a data safety monitoring board. Following approval by the institutional review boards of all participating centers, conduct and reporting will strictly adhere to national and international rules, regulations, and recommendations (e.g., Good Clinical Practice, data safety laws, and EQUATOR/CONSORT proposals)

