## Methods And Design

### Design

The ORCHID (Open Reduction and internal fixation versus Cast immobilization for Highly comminuted, Intra-articular fractures of the Distal radius) trial is a pragmatic, multi-center RCT that aims at evaluating differences in patient-centered outcomes between two major options (i.e., volar locked plating versus closed reduction and cast stabilization) for treating wrist fractures in an elderly population. 600 patients will be recruited at 15 hospitals of various levels of care and associated private practices throughout Germany. It is expected that 150 patients are recruited during the first year after the initiation of all centers, followed by recruitment of 300 and 150 patients in the subsequent years.

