### Statistical analysis

#### Sample size and power calculation

The sample size is based on the primary outcome variable and the primary analysis. In the German branch of the International Quality of Life Assessment (IQOLA) Project, the linear T-score transformed, US factor weighted PCS of the SF-36 score from 2525 subjects showed a mean of 50.6 with a standard deviation of 9.8[43]. Standard deviations of about 10 have been observed in studies of elbow fractures as well [51].

Different assumptions can be found about the minimally clinically relevant differences (MCRD) in SF-36 scales. The ORCHID investigators consider an MRCD of 8 points with a standard deviation of 30 clinically relevant. For the PCS scale with a standardized mean of 50 and a standard deviation of 10, this results in a MCRD of 8/3 = 2.67 points. This is close to Walters MCRD proposal of a clinically relevant difference of 2.5[52]. According to another statistical approach, the MCRD calculates to 2.83, accounting for a reported reliability coefficient of 0.92. Using a more conservative MCRD of 2.5 with a standard deviation of 10, 2 × 252 = 504 patients are needed to detect this difference with a power of 80% and a two-sided alpha of 5% with a test for means in independent samples.

The trial should also have sufficient power for the sensitivity analyses with the per-protocol-population. Incorporating 15% drop-outs (that is, deceased patients and losses to follow-up), a total sample size of n = 600 patients is needed.

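### The abstract gives 504 patients as the inclusion target, but the design and sample-size sections require 600; 504 is the number needed before drop-out

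*Protocol article*

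**What the plan says.** Three places in the protocol article give a number of patients for the trial.

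- **Abstract, Methods/Design:** "It is planned to include 504 patients in 15 participating centers throughout Germany over a three-year period". Drop-out is not mentioned there.
- **Methods and Design, Design:** "600 patients will be recruited at 15 hospitals of various levels of care and associated private practices throughout Germany". The yearly forecast follows: "150 patients are recruited during the first year after the initiation of all centers, followed by recruitment of 300 and 150 patients" in the later years.
- **Statistical analysis, Sample size and power calculation:** "Using a more conservative MCRD of 2.5 with a standard deviation of 10, 2 × 252 = 504 patients are needed", the calculation being made "with a power of 80% and a two-sided alpha of 5% with a test for means in independent samples". The next paragraph allows for 15% drop-outs, defined as deaths and losses to follow-up, and concludes that "a total sample size of n = 600 patients is needed".

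**The concern.** The abstract and the Design section describe the same quantity, namely patients entering the trial at 15 sites over three years, and give different numbers for it. The sample-size section shows that the abstract has picked up the intermediate result, before the drop-out allowance, and stated it as the number to include.

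The enrolment target determines when recruitment is complete, and it is a natural benchmark for judging the final report. With two published targets, a trial that closes near 504 could be described either as having reached its target or as having fallen 16% short (1 − 504/600 = 0.16). If 504 were acted on, the trial would lose the power for which it was sized once the expected losses occurred.

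**Working it through.** **Inputs, all from the sample-size section:** difference 2.5 PCS points; SD 10, so a standardised difference of 0.25; two-sided alpha 5%; power 80%; two independent means; equal arms; 15% drop-out.

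**1. Reproduce 504.** Per arm, by the normal approximation:

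n = 2 × (1.960 + 0.842)² / 0.25² ≈ 251.2, rounded up to 252; 2 × 252 = 504.

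The t-test version gives 252.1 per arm. The plan's 504 is reproduced, and it is the number required with an outcome.

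**2. Reproduce 600.** 504 / (1 − 0.15) = 593, which is consistent with 600 after rounding up. The yearly forecast agrees: 150 + 300 + 150 = 600.

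**3. Power under each enrolment figure after 15% loss.** Power ≈ Φ(0.25 × √(n/2) − 1.960), with n the number per arm who have an outcome.

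| Enrolled | Lost | With outcome | Per arm | Power (normal) | Power (t-test) |
|---|---|---|---|---|---|
| 504 | 0% | 504 | 252 | 80.1% | 80.0% |
| 504 | 15% | 504 × 0.85 = 428 | 214 | 73.5% | 73.3% |
| 600 | 15% | 600 × 0.85 = 510 | 255 | 80.6% | 80.4% |

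On the normal approximation, 504 enrolled with 15% lost falls 80.1 − 73.5 = 6.6 percentage points short of the power at 504 with no loss.

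**4. Sensitivity to the loss rate, 504 enrolled, difference 2.5 (normal approximation).**

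| Loss | Power |
|---|---|
| 5% | 78.1% |
| 10% | 75.9% |
| 15% | 73.5% |
| 20% | 70.9% |

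Each of these losses takes the 504 target below 80%.

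**5. Sensitivity to the difference.** At the protocol's less conservative value of 8/3 = 2.67 points, 504 enrolled with 15% lost gives 78.8%. The stated 80% is tied to 2.5 points.

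**The case against.** The strongest reply is that the planned trial is not underpowered. Both sections that govern the design say 600, the yearly forecast sums to 600, and nothing ties the end of recruitment to the abstract. The power loss arises only if someone acts on that one sentence. No calculation in the protocol is wrong, so this is a reporting inconsistency. All of that stands: the 73% is a conditional consequence and does not describe the design set out in the methods.

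A second reply is that 504 could be the intention-to-treat target, with the extra patients there to protect the per-protocol analysis, which the sample-size section mentions just before the inflation. It also notes that the protocol does not itself call 504 the evaluable number. This reading is weaker. The 15% is defined as deaths and losses to follow-up, and those patients also lack a 12-month PCS for the primary analysis. Multiple imputation is planned only where suitable, and in general it does not restore the information lost. Even on this reading the required total is still 600.

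A third reply is that the primary analysis is an ANCOVA with centre, fracture type, gender and age, which may recover precision. It may, but restoring 80% with 428 patients needs covariates that explain about 15% of the PCS variance (1 − 428.4/504 = 0.15). The protocol assumes no such gain and sizes the trial on an unadjusted comparison.

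Finally, an abstract may condense. That excuses leaving out the drop-out allowance; it does not excuse stating a different number to be included.

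**Conclusion.** The concern holds. The abstract's 504 contradicts the 600 in the Design and sample-size sections, and nothing in the article reconciles them. The derivation identifies 600 as the number to enrol and 504 as the number needed with a 12-month PCS. Enrolling only 504 would give about 73% power in place of 80%. That figure rests on the protocol's own difference of 2.5, SD 10 and 15% loss, on an unadjusted two-sample test, and on no information being recovered for patients without a 12-month PCS. The design in the body of the article keeps its stated power. The correction should be made because the sample size is a figure on which the trial relies, and the published target should not be ambiguous.

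**What to change.** Replace the sentence in the abstract with wording such as: *It is planned to randomise 600 patients in 15 centres in Germany over three years (504 are needed with an evaluable 12-month PCS; the total allows for 15% drop-out).* Use 600 as the single recruitment target wherever one is stated, and label 504 in the sample-size section as the number required with an evaluable primary outcome.

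The cost is a sentence in the abstract and a short label in the sample-size section. No patients are added, because 600 is already the design figure, and neither the analysis nor the recruitment forecast changes.

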**Discussion:**

To our knowledge, ORCHID is the first multicenter RCT designed to assess quality of life and functional outcomes following operative treatment compared to conservative treatment of complex, intra-articular fractures of the distal radius in elderly patients. The results are expected to influence future treatment recommendations and policies on an international level.

**Trial registration:**

ISRCTN: ISRCTN76120052

Registration date: 31.07.2008; Randomization of first patient: 15.09.2008

## Background

Distal radial fractures represent the most common injuries in humans and make up a considerable workload in orthopaedic and surgical departments worldwide. In population-based investigations, incidence rates vary from 5.7 to 124.6 per 10,000 person-years[1-21]. Together with fractures of the proximal humerus, vertebral bodies and the proximal femur, fractures of the distal radius typically mark the onset of symptomatic osteoporosis[22-24].

Established treatment options comprise closed reduction and cast stabilization, external fixation, and open reduction with internal plate fixation (ORIF). The first two options may be combined with percutaneous K-wire pinning.

According to a Cochrane Review of randomized controlled trials (RCT) and later clinical investigations[25-27], the most effective, efficient, and safe method of treating complex intraarticular wrist fractures remains unclear.

To date, a single RCT has compared ORIF to casting (19 and 23 patients, respectively) [28], suggesting a higher likelihood of excellent function with ORIF than with closed reduction (risk ratio [RR] 0.69, 95% confidence interval [CI] 0.48 - 1.00). The same trial also compared ORIF to external fixation (19 and 18 patients), without any difference in the rates of excellent function (RR 0.95, 95% CI 0.59 - 1.52). Two trials in 2004 and 2005 suggest better functional outcomes with external fixation compared to internal fixation with dorsal Pi-plates [29-31].

In recent years, angle-stable, volar locking plates have been propagated and enthusiastically used for surgical fixation of distal radial fractures, especially in the osteoporotic bone. The underlying biomechanical principle of angle-stable locked plating is that uni-cortical, threaded screws fixed in the screw hole of the plate ("internal fixator") reduce shear forces, thereby preventing loosening of the surgical construct. However the available clinical evidence in favor of this principle is limited to case series of moderate to poor quality [32-38].

The currently largest reported series of 114 patients also signals high complication rates with volar locking plate fixation of complex wrist fractures. Although functional outcomes after one year were reasonable, 31 patients (27%, 95% CI 19 - 36%) faced complications, mainly tendon irritation, carpal tunnel syndrome, and complex regional pain syndrome (CRPS) [39].

Regardless of these critical reports, volar locked plating has emerged as the surgical standard of care for managing distal radial fractures in Europe and the US[40].

## Study Rationale

Closed reduction and plaster casting is an ubiquitous, simple, safe, and cost-effective intervention to treat distal radial fractures. Casting may be applied in an outpatient setting but causes the discomfort of four to six weeks of immobilization of the wrist. In contrast, ORIF needs a hospital environment, well equipped operating rooms, and costly surgical material, but allows for early mobilization without cast immobilization.

Comminuted intraarticular wrist fractures (type 23 C1, C2, C3 according to the common classification rules of the AO Foundation [AO/ASIF] and the Orthopaedic Trauma Association [OTA]) destroy cartilage layers and compromise joint integrity (Figure 1). Biological fracture treatment aims at restoring the axis and length of the injured bone, reconstructing the articular surface, and achieving a stable construct that allows for early mobilization and weight bearing. However, excessive reconstruction with technically demanding and time consuming fixation of multiple small fragments may produce more good than harm, especially in the osteoporotic bone, osteoarthritis of the radio-carpal and adjacent joints, and poor skin and soft tissue conditions.

**Figure 1 F1:**
[figure not shown]
**AO/ASIF-classification**. AO/ASIF-classification of intraarticular distal radius fractures (C1,C2,C3)

Thus, the obvious biomechanical advantages with internal fixation (anatomic reposition and stable fixation) must be balanced against its potential biological disadvantages (violation of the skin-soft tissue-bone-compound).

Given the high costs of this surgical intervention and taking into account its so far unproven benefits for elderly patients, there is an urgent need for a large, multi-center RCT comparing operative with non-operative treatment. This trial should clarify whether the anticipated benefits with ORIF hold against its invasiveness, potential complications, and costs.

## Primary Hypothesis

Because of previous studies and international trends in health services research, the investigators consider the Short Form 36 (SF-36) Physical Component Score (PCS) as the key outcome of this trial. They assume that, based on data from other studies, a difference of 8 points (on a scale of 50) with a pooled standard deviation (SD) of 3 (leading to a standardized mean difference of 8/3 = 2.67) between the experimental and the control intervention is of both clinical and health-political interest. As there are still no generally accepted 'minimum clinically important differences' (MCID) of the SF36-PCS in patients with fractures of the long bones, the predefined MCID was mainly based on the widely used SEM criterion [41]

*The primary hypothesis is that, after a follow-up of one year, there is a clinically relevant standardized mean difference of 2.67 points in the SF-36-PCS between surgical and non-surgical treatment of intra-articular fractures of the distal radius in elderly patients*.

## Methods And Design

### Design

The ORCHID (Open Reduction and internal fixation versus Cast immobilization for Highly comminuted, Intra-articular fractures of the Distal radius) trial is a pragmatic, multi-center RCT that aims at evaluating differences in patient-centered outcomes between two major options (i.e., volar locked plating versus closed reduction and cast stabilization) for treating wrist fractures in an elderly population. 600 patients will be recruited at 15 hospitals of various levels of care and associated private practices throughout Germany. It is expected that 150 patients are recruited during the first year after the initiation of all centers, followed by recruitment of 300 and 150 patients in the subsequent years.

### Eligibility criteria

Men and women aged 65 years or older with an isolated, unilateral, closed, comminuted, intra-articular fracture of the distal radius (AO/OTA 23 C1, C2, C3) according to the judgment of the surgeon on call are enrolled onto the trial.

To avoid misclassification of exposure, all radiographs will be evaluated centrally and independently by an orthopaedic surgeon and a radiologist. In case of disagreement there will be a consensus evaluation.

Only patients with a maximum interval of one week between injury and intervention must be included. No specific surgical pre-treatment (i.e., K-wiring, external fixation) is allowed. Patients must be able to understand the meaning of the trial and its consequences. Written informed consent or verbal agreement in presence of a witness in case of a fracture of the dominant hand and inability to write is mandatory for trial inclusion.

Patients will be excluded if the responsible surgeon requests surgical treatment, especially in case of open fractures or other situations in which the principle of therapeutic uncertainty (equipoise) is violated.

Also, patients with a high risk of anaesthesiology problems (i.e., ASA risk score > 3), acute infection, extreme obesity (i.e., BMI > 35 kg/m²), mental illness or low expected compliance will be excluded from trial participation. If patients issue a certain treatment preference, they will be excluded as well.

### Randomization

After having agreed with trial participation, patients will be randomized by the responsible surgeon to one of the treatment arms, using a web-based randomization tool (http://www.randomizer.at). Randomization is performed by blocks with stratification for participating centers.

### Interventions

Patients must be included only if there was no specific (i.e., physician-performed or -prescribed) pretreatment within one week after a traumatic exposure to the wrist.

All fractures will initially be reduced under image-intensifier control, followed by plaster cast stabilization (Figure 2 and 3). The intervention is performed by the surgeon on charge with proven expertise in reduction and casting maneuvers. Centers may follow their preferred reduction and casting techniques and locally established interventions for pain management (i.e., fracture block or intravenous pain medication).

**Figure 2 F2:**
[figure not shown]
**Closed reduction and casting**. Closed reduction and casting of an intraarticular distal radius fracture in the finger-trap traction technique with a light cast.

**Figure 3 F3:**
[figure not shown]
**Post-reduction radiograph of the wrist**. Mild shortening of radial length in the anteroposterior view after casting

#### Non-operative treatment

If randomized to non-operative care, cast treatment will be continued for six weeks. Once swelling has decreased, the splint cast is converted into a closed cast (hard plaster or light cast). Patients in the non-operative arm are usually treated in an ambulatory setting.

#### Operative treatment

If randomized to operative treatment, patients will be admitted to the hospital and operated on as early as possible, depending on local tissue conditions, hematoma and swelling and suitability of the patient for anaesthesia.

ORIF will be performed via a volar approach and using angle stable locking plates (Figure 4, 5 and 6). The protocol does not mandate certain hardware. ORIF is performed under plexus or general anesthesia and fluoroscopic guidance. All surgeons performing the operation have proven expertise with the procedure and are familiar with the used implants. Post-operative cast stabilization of the wrist may not exceed two weeks.

**Figure 4 F4:**
[figure not shown]
**Intraarticular distal radius fracture**. Anteroposterior radiograph of an intraarticular distal radius fracture type C1-AO/ASIF

**Figure 5 F5:**
[figure not shown]
**Operative treatment**. Postoperative radiograph shows restoration of radial length

**Figure 6 F6:**
[figure not shown]
**Operative treatment**. Lateral wrist radiograph shows restoration of palmar inclination

### Outcome measures

#### Primary outcome

The primary objective of ORCHID is to compare patient-reported outcomes like function, independence and health-related quality of life, measured with the Short Form 36 (SF-36) Physical Component Score (PCS), after operative and non-operative treatment of comminuted wrist fractures rather than surrogate measures (i.e., radiographic healing).

The Short Form 36 (SF-36) is the most widely used generic health assessment questionnaire worldwide. Its validity and suitability to describe wellbeing in a broad range of clinical conditions from a patient's point of view has been studied extensively[41-44].

#### Secondary outcomes

Another quick and validated tool is the EuroQol-5D (EQ-5D). Health utility measures can easily be derived from this instrument, allowing for later health-economic analyses. With the EuroQol-5D the outcomes of the two treatment arms can be compared and health-related quality of life can be measured.

In addition to generic forms, the 30-item, self-reported Disability of the Arm, Shoulder and Hand Score (DASH) questionnaire will be employed as a disease-specific outcome measure.

The DASH was selected as the preferred specific outcome tool because of the longer experience gained with this instrument in Germany. Cross-cultural validation started as early as 2003 [45]. DASH is the recommended tool for outcome assessment in the national clinical guideline for managing fractures of the distal radius http://www.uni-duesseldorf.de/AWMF/ll/012-015.htm and shows comparable psychometric properties to the Patient-Rated Wrist Evaluation PRWE in evaluating recovery after a distal radius fracture[46].

The SF-36, the DASH and the EuroQol-5D are assessed as patient completed questionnaires with assistance of a study nurse during the stay in the clinic or at the outpatient visit.

Wrist function in terms of range of motion (ROM) will be measured using a goniometer. Finally, we will address the patients' independence and ability to cope with everyday activities, nursing home admissions and the need for assistance in activities of daily living, and mortality. Complications (e.g., loss of reduction, hardware failure and misplacement, wound healing problems, infections, revisions, neurologic impairment, pressure ulcera and others) as well as serious adverse events (SAE) will be recorded throughout the study, and regularly evaluated by a Data Safety Monitoring Board (DSMB).

